### Power Analysis

The primary outcomes are treatment engagement, depression symptom change in PHQ-9 score, and depression remission on the Mini International Neuropsychiatric Interview (MINI). We compare the means in a regression framework, after taking into account the design effect induced by clustering, to determine the power when comparing the intervention group to the control group. We note that the end-status analysis assumed for the power calculations can be conservative because it does not use all 3 waves of data and uses only the projected retained sample at month 12. For the power analyses, we used the conservative estimate of the projected retention rate of 79% at the 12-month follow-up. This translates to approximately 64 patients per condition at the 12-month follow-up. A recent meta-analysis found an effect size of 0.78 favoring therapies using BA over control conditions using professionals [40]. However, given the use of paraprofessionals with limited mental health training, we expect smaller effect sizes. For these power analyses, we used conservative effect sizes of 0.3 and 0.4. Since patients are clustered within intervention groups, patients’ outcomes may be correlated, even though other randomized mental health studies have found intraclass correlation coefficients that are essentially zero [41]. Using this effect size, a power of 0.85, a conservative intracluster correlation of 0.1, a cluster size of 10, and a design effect of at least 2, we determined that 142 participants were needed for the study. Calculations were performed using sampsi and sampclus commands on STATA [42]. To account for loss to follow-up, we planned to enroll 160 and ended up with a final sample size of 166 participants.

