### Data Analysis

The data will be analyzed with an intention-to-treat approach for all outcomes. We will conduct a longitudinal regression analysis [49] to compare the two interventions on (1) primary outcomes, including depression scores based on the PHQ-9 and remission from depression (based on MINI diagnoses), and (2) secondary outcomes, including BA, functioning, quality of life, treatment acceptance, and economic outcomes. To address internal validity concerns of a nonrandomized design, we will use propensity score-based weighting, which is a recommended statistical technique to equate groups on a large number of baseline covariates to adjust for potential baseline differences and strengthen the inferential pathway toward causation in nonrandomized design [50-52]. Propensity score weights will be calculated using baseline demographic and clinical characteristics such as the PHQ-9, the GAD-7, physical health functioning, mental health functioning, BA, social support, self-efficacy, mental health literacy, age, education, economic status, work status, marital status, and loan exposure.

A regression analysis [49] with propensity weights will be conducted to estimate treatment effect with repeated measures of our outcomes at 3 time points accounting for demographic covariates, such as age, marital status, baseline income variables, work status, baseline mental health, functioning, and social predictors. Effects may vary over 6 and 12 months; therefore, we will also test for linear time trends in the regression models. Outcomes for patients enrolled from the same intervention group, cohort, and site may be correlated. Ignoring this clustering effect would lead to the underestimation of the variance of treatment effects. Thus, we will adjust for group clustering to account for the correlation among the measures of patients enrolled in the same intervention group, cohort, and site [53].

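### The single stated power of 0.85 comes from a comparison of means yet stands over a primary set that includes binary MINI remission; the stated inputs do not deliver it for remission, nor for the PHQ-9 mean

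*Protocol article*

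**What the plan says.** The Power Analysis section opens with the outcome set: "The primary outcomes are treatment engagement, depression symptom change in PHQ-9 score, and depression remission on the Mini International Neuropsychiatric Interview (MINI"). The basis of the calculation follows at once: "We compare the means in a regression framework, after taking into account the design effect induced by clustering". The effect is standardised: "For these power analyses, we used conservative effect sizes of 0.3 and 0.4". The other inputs are "a power of 0.85, a conservative intracluster correlation of 0.1, a cluster size of 10, and a design effect of at least 2", and the result is "we determined that 142 participants were needed for the study".

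Retention is taken as "the conservative estimate of the projected retention rate of 79% at the 12-month follow-up", which the section turns into about 64 women per condition. On recruitment it says "we planned to enroll 160 and ended up with a final sample size of 166 participants".

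The Data Analysis section keeps both depression outcomes as "primary outcomes, including depression scores based on the PHQ-9 and remission from depression (based on MINI diagnoses"), and sets a two-sided 5% significance level. The Abstract describes the second of these as remission rates at 6 and 12 months. The article gives no expected remission rate for either arm and no calculation for proportions.

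**The concern.** Remission is a yes/no outcome compared as rates. A power derived from means and a standardised mean difference does not carry over to it unless someone says how the effect is converted and what the comparison-arm rate is. The article says neither, yet one power and one sample size stand over the whole primary set.

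At stake is how a null remission result will be read. Enrolment is complete and the analysis is under way. If the trial is thought to have 85% power for a modest effect on every primary outcome, a non-significant remission comparison may pass for evidence of no effect, when the retained sample could reliably show only a large difference.

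**Working it through.** **Inputs.** From Power Analysis: d = 0.3 and 0.4; power 0.85; intracluster correlation 0.1; cluster size 10; design effect (DE) at least 2; about 64 per arm at month 12; 142 needed. From Data Analysis: two-sided 0.05. Assumed: equal arms, and E-TAU remission of 30-60%. The formula DE = 1 + (10 - 1) × 0.1 gives 1.9, so 1.9 and 2 are both shown, with 1 for no clustering.

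**Step 1: the plan's own figure.** Total N = 4 × (1.960 + 1.036)² × DE / d² = 4 × 8.978 × DE / d².

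| | DE 1 | DE 1.9 | DE 2 |
|---|---|---|---|
| d = 0.4 | 224 | 426 | 449 |
| d = 0.3 | 399 | 758 | 798 |

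The stated 142 is not reproduced. It matches d of about 0.50 with no clustering, or 0.69-0.71 with DE 1.9-2.

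**Step 2: power for means at 64 per arm.** Power = Φ(d × √(64 / (2 × DE)) - 1.96).

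| | DE 1 | DE 1.9 | DE 2 |
|---|---|---|---|
| d = 0.4 | 0.62 | 0.38 | 0.36 |
| d = 0.3 | 0.40 | 0.23 | 0.22 |

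At the full 142 (71 per arm) and DE 1.9, power is 0.41 and 0.25.

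**Step 3: power for remission at 64 per arm, d = 0.4.** Power = Φ(|p2 - p1| / √(DE × [p1(1 - p1) + p2(1 - p2)] / 64) - 1.96), where p1 is E-TAU remission and p2 is obtained in three ways:
- Logistic: odds ratio = exp(0.4 × π / √3) = 2.07.
- Probit: p2 = Φ(Φ⁻¹(p1) + 0.4).
- Cohen h = 0.4 on the arcsine scale.

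| Conversion | p2 for p1 = 0.30 / 0.40 / 0.50 / 0.60 | Power, DE 1 | Power, DE 2 |
|---|---|---|---|
| Logistic | 0.47 / 0.58 / 0.67 / 0.76 | 0.48-0.54 | 0.27-0.31 |
| Probit | 0.45 / 0.56 / 0.65 / 0.74 | 0.42-0.44 | 0.23-0.25 |
| Cohen h | 0.49 / 0.60 / 0.69 / 0.78 | 0.63 | 0.37 |

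No cell reaches 0.85. Under the logistic and probit conversions remission has less power than the mean (0.62 and 0.36). Under Cohen h it has the same.

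**Step 4: the same comparison at the N that gives means 0.85** (d = 0.4, DE 2, about 449 in total). Remission power is 0.72-0.78 (logistic), 0.64-0.67 (probit) and 0.86 (Cohen h).

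**Step 5: detectable remission difference, with no effect-size conversion.** Solving the Step 3 formula for p2 at power 0.85 and 64 per arm:

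| E-TAU remission | DE 1 | DE 2 |
|---|---|---|
| 30% | 55% (25 points) | 65% (35 points) |
| 40% | 66% (26 points) | 75% (35 points) |
| 50% | 75% (25 points) | 83% (33 points) |
| 60% | 83% (23 points) | 90% (30 points) |

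**The case against.** **The article never says in so many words that remission has 85% power.** It states openly that means are compared, and a two-proportion calculation might sit in a fuller document. That is fair as far as it goes, and the absence of such a calculation would not on its own be a finding. But the section introduces its power with a primary set that includes remission and limits the figure nowhere. What the article states is therefore wrong for one member of that set.

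**The clustering allowance may be pessimistic.** The article calls an intracluster correlation of 0.1 conservative, cites values near zero elsewhere, and notes that an end-status calculation ignores the other waves. With no clustering at all, remission power is still only 0.42-0.63. Repeated measures and covariate adjustment may help, but the article does not quantify the gain, and the stated 0.85 is an end-status figure. For the PHQ-9, even a baseline correlation of 0.8 at d = 0.4 and DE 1.9 would need 426.5 × (1 - 0.64) = 154, still above 142.

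**A reader might infer that remission falls short of 85% at any sample size that gives the PHQ-9 mean 85%.** The documents do not support that. They specify no conversion from d to proportions, and under Cohen h nothing is lost (0.86 in Step 4). The text leans towards a standardised mean difference, since Data Analysis plans Cohen d for all outcomes, but that does not settle how the effect carries to a rate.

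**A reader might also treat remission as the PHQ-9 cut at a threshold, with power lost by dichotomising.** It is not: it rests on MINI diagnoses, a separate measure. Table 2 shows the two can diverge. At baseline the arms are close on PHQ-9 (14.54 vs 14.28), while MINI depression differs (84, 91.30% vs 57, 78.08%; odds ratio (84 × 16) / (57 × 8) = 2.9). The effect on remission may be larger or smaller than that on PHQ-9, so d = 0.4 for remission is an illustration.

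**Conclusion.** The point holds in this form: the 0.85 stands over a primary set that includes MINI remission, and the stated inputs do not deliver it for remission under any of the three conversions. At 64 per arm and an effect equivalent to d = 0.4, remission power is about 0.42-0.63 without clustering and 0.23-0.37 at design effect 2. How far remission trails the mean is not fixed by the documents and may be nil.

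It would be equally wrong to conclude that 0.85 is sound for the PHQ-9 and only needs confining to it. Steps 1 and 2 show that it fails there too.

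The detectable difference is the firmest result because it needs no conversion. It rests on the assumed E-TAU remission of 30-60%, equal arms, a normal approximation, and all 64 women per arm counting towards remission. Table 2 shows 141 women with current MINI depression at baseline; if only those women can remit, the numbers are smaller and power is lower.

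**What to change.** - Do not attach 0.85 to the PHQ-9 mean. Restate the power for means as the stated inputs and retained sample give it: at 64 per arm, 0.36-0.38 for d = 0.4 and 0.22-0.23 for d = 0.3 with design effect 1.9-2. If other inputs produced 142, state them.
- State that the comparison-of-means calculation does not cover remission.
- Add a two-proportion calculation for remission at the retained sample with the same design effect. Report it as the difference detectable with 85% power over a stated range of assumed E-TAU remission. For 30-60% this is about 30-35 percentage points at design effect 2 and about 23-26 points without clustering, with the range labelled as an assumption.
- State that a non-significant remission result will be interpreted from its confidence interval and not as evidence of no effect.

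The cost is some wording and one calculation. No new patients are needed and the planned analysis does not change. The downside is that the stated sensitivity becomes less favourable for both depression outcomes.

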We will examine variable distributions from all time points to assess missing data patterns within each study wave and replace them with information gathered from clinic logs and program records. Based on previous similar studies in Vietnam in general and Da Nang in particular, we expect response rates of approximately 80% at 6-month and 12-month follow-ups, resulting in about 128 patients at the 2 follow-ups. All planned analyses will use likelihood methods, which are effective under missing at random assumptions [54]. This approach helps account for participants dropping out of the study while making the most efficient use of all the data collected. Because time will be a random effect within the mixed model analyses, participants without complete data will be included fully in the analyses. For all outcomes, Cohen *d* will be calculated to estimate the effect size using pooled SD of baseline scores. Two-sided *P*<.05 will be considered statistically significant.

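### The requirement of 142 participants does not follow from the power analysis's own inputs, and 160 enrolled at 79% retention does not leave 142

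*Protocol article*

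**What the plan says.** The Power Analysis section assumes a comparison of means at month 12 in the retained sample. It notes a meta-analytic effect of 0.78, sets it aside because the providers are paraprofessionals, and says "we used conservative effect sizes of 0.3 and 0.4". The calculation then reads "Using this effect size, a power of 0.85, a conservative intracluster correlation of 0.1", followed by "a cluster size of 10, and a design effect of at least 2, we determined that 142 participants were needed for the study".

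On attrition, the section takes 79% retention at 12 months and says "This translates to approximately 64 patients per condition at the 12-month follow-up", which is 128 in total. It then says that, to allow for losses, "we planned to enroll 160 and ended up with a final sample size of 166 participants". The Data Analysis section repeats a figure of about 128 at follow-up, there with roughly 80% response.

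The power paragraph gives no significance level. The Data Analysis section says "Two-sided *P*<.05 will be considered statistically significant".

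**The concern.** A reader takes from this paragraph that 142 evaluable women give 85% power for a standardised difference of 0.3 to 0.4, and that 160 enrolled would secure that number. Neither step agrees with the figures printed beside it. The shortfall is visible before any clustering is allowed for, and the projected follow-up sample (128) is below the stated requirement (142) within the same paragraph.

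What is at stake is interpretation. Data collection ended in September 2015 and the analysis is in progress, so the sample is fixed. If the power claim stands, a non-significant primary result could be taken as good evidence that an effect of 0.3 to 0.4 is absent, which the design would not support.

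**Working it through.** **Inputs.** From Power Analysis: d = 0.3 and 0.4 (SD = 1), power 0.85, ICC 0.1, cluster size 10, design effect (DE) at least 2, retention 79%, 64 per arm at month 12, 142 required, 160 planned, 166 enrolled. From Data Analysis: two-sided 5%, assumed to apply to the power calculation as well.

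**Design effect.** 1 + (10 − 1) × 0.1 = 1.9, so both 1.9 and 2 are used below. If only LIFE-DM is clustered, the average over equal arms is (1.9 + 1)/2 = 1.45.

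**Attempt to reproduce 142.** Total N = 2 × DE × 2(1.960 + 1.036)²/d². Before clustering this is 2 × 112.2 at d=0.4 and 2 × 199.5 at d=0.3.

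| Clustering | d = 0.4 | d = 0.3 |
|---|---|---|
| None (DE 1) | about 225 | about 399 |
| LIFE-DM only (DE 1.45) | about 325 | about 579 |
| Both arms (DE 1.9 to 2) | about 426 to 449 | about 758 to 798 |

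Rounding up to whole women per arm before applying DE adds only a few (for example 226 and 430 to 452 at d=0.4). One-sided 5% does not rescue the figure: 180 and 320 before clustering. Nor does d = 0.78, which gives 114 to 120 at 85% power with DE 1.9 to 2.

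Run backwards at 85% power, 71 per arm corresponds to d = 2.996 × √(2 × DE/71): about 0.50 (DE 1), 0.61 (DE 1.45), 0.69 (DE 1.9) or 0.71 (DE 2). None is a stated planning effect.

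**Attrition.**
- 160 × 0.79 = 126.4 (128 at 80%).
- 166 × 0.79 = 131.1.
- 142/0.79 = 179.7, so 180 would have to be enrolled.
- 142/160 = 0.8875, so the step from 142 to 160 allows about 11% loss, against the assumed 21%.

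**Power with 64 per arm, month-12 comparison.** Power = Φ(d/√(2 × DE/64) − 1.960). Detectable d at 85% power = 2.996 × √(2 × DE/64).

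| Clustering | d = 0.3 | d = 0.4 | d detectable at 85% |
|---|---|---|---|
| None (DE 1) | 40% | 62% | 0.53 |
| LIFE-DM only (DE 1.45) | 29% | 47% | 0.64 |
| Both arms, DE 1.9 | 23.3% | 37.5% | 0.73 |
| Both arms, DE 2 | 22.4% | 35.9% | 0.75 |

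The actual 74/92 split at 79% retention barely changes the last two rows (about 23–24% and 36–38%). Even with a full 142 evaluable and DE 1.9 to 2, power would be about 24–25% and 39–41%.

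**The case against.** The strongest objection is that these are not the trial's actual power. The section itself says the end-status analysis can be conservative, calls its ICC conservative, and cites studies with intraclass correlations near zero. The planned model uses three waves, baseline covariates and likelihood methods that keep incomplete cases. This stands. The documents give no baseline-to-12-month correlation, so any gain rests on an assumed one. With DE 1.9 to 2 and 64 per arm, a correlation of 0.3, 0.5 or 0.7 gives power of about 24–41%, 28–47% or 39–63% across the two effect sizes. With no clustering at all, 0.5 gives about 50–74% and 0.7 about 66–89%, so 85% is passed only at d=0.4 with a high correlation and zero ICC. Propensity weighting and correlation within only four sites would tend to lower power and are not in the calculation.

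Second, clustering may apply to one arm only: the plan describes therapy groups in LIFE-DM and none in E-TAU. That is a fair reading and is shown above. It eases the shortfall without removing it. Since Data Analysis also mentions cohort and site clustering, the structure is open.

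Third, a reader might infer that the design effect of 2 is an error to be corrected to 1.9. It is better seen as cautious rounding, worth about 5% in N. Varying group sizes and site correlation could push the true value above 1.9.

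Finally, the plan already intends to report Cohen d and describes its findings as estimates of real-world effectiveness, which limits the risk of misreading. It does not make the power statement correct.

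**Conclusion.** The stated requirement is wrong on its own inputs. No reading that keeps d = 0.3 or 0.4 and 85% power yields 142. The smallest two-sided total is about 225, and with the stated design effect the requirement is about 3.0 to 5.6 times 142 (426/142 to 798/142). The attrition step is inconsistent without any statistical assumption: 126 to 131 retained against 142 required.

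The size of the power shortfall depends on assumptions: two-sided 5%, an unadjusted month-12 comparison, 64 per arm, and where the clustering lies. On those terms power is 22–37.5% with clustering in both arms and at most 62% with none.

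A reader might go further and infer that this range is the trial's real power, or that the trial could not detect its planned effect. The documents do not support either. The longitudinal model may do better and the weighting may do worse, and low power is not zero power. What is supported is that the paragraph's claim of 0.85 at 0.3 to 0.4 should not stand, and that a non-significant result should not be read as evidence of no effect of that size.

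**What to change.** Text only; no added enrolment, and no change to the estimand or model.

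1. Recover the inputs of the original sampsi/sampclus run and say which effect size the 142 rests on. Then correct or withdraw the claim that 142 gives 0.85 power at 0.3 to 0.4.
2. Correct the attrition sentence: at 79% retention, 142 evaluable needs about 180 enrolled; 160 leaves about 126 and 166 about 131.
3. State power under the section's own month-12 assumptions with 64 per arm: about 22–23% at d=0.3 and 36–37.5% at d=0.4 with a design effect of 1.9 to 2, and 85% power only at d of about 0.73 to 0.75. Give the alternatives: 29% and 47% (detectable d 0.64) if only LIFE-DM is clustered; 40% and 62% (0.53) with no clustering.
4. Add that the baseline-adjusted longitudinal model may raise these figures, and that propensity weighting and correlation within four sites may lower them. The design effect of 2 may stay as a cautious rounding.
5. Say that a non-significant primary result will not be interpreted as evidence against an effect of 0.3 to 0.4.

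The cost is a rewritten paragraph and a much less favourable power statement.

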### Outcome Measures

All study measures (Table 1) were adapted using a consensus approach to ensure linguistic and cultural appropriateness for use in Vietnam. Primary outcomes focused on depression severity and diagnosis, measured by the PHQ-9 [38], which assesses depressive symptom severity, and severe mental illness screener, which was based on items from the MINI [43]. Secondary outcomes included program participation indicators, such as group attendance, engagement in livelihood activities, and acceptance of depression care. The data were gathered through face-to-face surveys, clinic logs, and program records.

**Table 1. T1:** Main outcome measures.

Indicator	Scale or measure	Data source
Depression severity	Patient Health Questionnaire	Surveys at baseline, 6 months, and 12 months
Anxiety severity	Generalized Anxiety Disorder	Surveys at baseline, 6 months, and 12 months
Health functioning	Short-form Health Survey	Surveys at baseline, 6 months, and 12 months
Quality of life	Quality of Life Enjoyment and Satisfaction Questionnaire	Surveys at baseline, 6 months, and 12 months
Behavioral activation	Brief Activation for Depression Scale–Short Form	Surveys at baseline, 6 months, and 12 months
Social capital	Short Social Capital Assessment Tool	Surveys at baseline, 6 months, and 12 months
Program participation	Group attendance, engagement in livelihood activities, and acceptance of depression care	Clinic logs or program records

Anxiety symptoms were assessed using the 7-item Generalized Anxiety Disorder 7 scale (GAD-7) [44]. Health functioning was measured by the Short Form-12 Health Survey [45], capturing both physical and mental health status. Quality of life was assessed with the Quality of Life Enjoyment and Satisfaction Questionnaire [46], while BA was evaluated using the Brief Activation for Depression Scale–Short Form [47], which captures levels of engagement in goal-directed activities. Social capital was measured using an adapted version of the Short Social Capital Assessment Tool [48], which includes indicators of community participation and support. Economic and employment outcomes included measures of work status, income, household assets, loan and savings activities, and perceived performance of small businesses. Additional sociodemographic covariates such as age, marital status, education, mental health literacy, household size, and number of dependents were also collected to adjust for potential confounders.

### Data Analysis

The data will be analyzed with an intention-to-treat approach for all outcomes. We will conduct a longitudinal regression analysis [49] to compare the two interventions on (1) primary outcomes, including depression scores based on the PHQ-9 and remission from depression (based on MINI diagnoses), and (2) secondary outcomes, including BA, functioning, quality of life, treatment acceptance, and economic outcomes. To address internal validity concerns of a nonrandomized design, we will use propensity score-based weighting, which is a recommended statistical technique to equate groups on a large number of baseline covariates to adjust for potential baseline differences and strengthen the inferential pathway toward causation in nonrandomized design [50-52]. Propensity score weights will be calculated using baseline demographic and clinical characteristics such as the PHQ-9, the GAD-7, physical health functioning, mental health functioning, BA, social support, self-efficacy, mental health literacy, age, education, economic status, work status, marital status, and loan exposure.

A regression analysis [49] with propensity weights will be conducted to estimate treatment effect with repeated measures of our outcomes at 3 time points accounting for demographic covariates, such as age, marital status, baseline income variables, work status, baseline mental health, functioning, and social predictors. Effects may vary over 6 and 12 months; therefore, we will also test for linear time trends in the regression models. Outcomes for patients enrolled from the same intervention group, cohort, and site may be correlated. Ignoring this clustering effect would lead to the underestimation of the variance of treatment effects. Thus, we will adjust for group clustering to account for the correlation among the measures of patients enrolled in the same intervention group, cohort, and site [53].

We will examine variable distributions from all time points to assess missing data patterns within each study wave and replace them with information gathered from clinic logs and program records. Based on previous similar studies in Vietnam in general and Da Nang in particular, we expect response rates of approximately 80% at 6-month and 12-month follow-ups, resulting in about 128 patients at the 2 follow-ups. All planned analyses will use likelihood methods, which are effective under missing at random assumptions [54]. This approach helps account for participants dropping out of the study while making the most efficient use of all the data collected. Because time will be a random effect within the mixed model analyses, participants without complete data will be included fully in the analyses. For all outcomes, Cohen *d* will be calculated to estimate the effect size using pooled SD of baseline scores. Two-sided *P*<.05 will be considered statistically significant.

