### Study Design

A matched-pair cluster nonrandomized controlled trial was conducted, comparing the LIFE-DM intervention with E-TAU. Two CHSs were allocated to the LIFE-DM group intervention and 2 to the E-TAU arm, which offered guideline-based antidepressant medications. Cluster-level randomization was not feasible for two reasons: (1) the small number of available sites limited the use of randomization for achieving balance and (2) the WU, whose infrastructure was essential for delivering the microfinance component, imposed operational constraints on random assignment of microfinance services across sites. To strengthen comparability in the absence of randomization, CHSs were matched on key characteristics prior to allocation (see the *Study Site Characteristics and Recruitment* section), and within each matched pair, 1 site was assigned to LIFE-DM and the other to E-TAU.

The trial was designed to approximate real-world implementation conditions under which the program would be disseminated, in order to assess the feasibility and effectiveness in routine care settings. Although propensity score matching will be used to reduce baseline imbalances, we acknowledge that selection bias may still be present due to the nonrandomized cluster allocation and potential unmeasured confounding at both individual and cluster levels.

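### The trial allocated four health stations (2 vs 2, in matched pairs), but the 85% power rests on therapy groups of 10, and no inference suited to four clusters is stated

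*Protocol article*

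**What the plan says.** **Allocation.** Under Study Design, the unit is the CHS: "Two CHSs were allocated to the LIFE-DM group intervention and 2 to the E-TAU arm". The stations were matched first, and "within each matched pair, 1 site was assigned to LIFE-DM and the other to E-TAU".

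**Power.** The Power Analysis section uses a different unit: "Since patients are clustered within intervention groups", outcomes may be correlated. It then takes "a conservative intracluster correlation of 0.1, a cluster size of 10, and a design effect of at least 2", with "a power of 0.85", and on effect size: "we used conservative effect sizes of 0.3 and 0.4". The result is 142 participants needed, 160 planned and 166 enrolled, with about 64 per arm expected at 12 months. Neither the station nor the pair enters.

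**Analysis.** The Data Analysis section says that outcomes may be correlated within intervention group, cohort and site, and then: "we will adjust for group clustering to account for the correlation among the measures of patients enrolled in the same intervention group". The same sentence continues to cohort and site, so site is named. The section specifies likelihood-based mixed models, names time as the only random effect, and says that a two-sided P below .05 "will be considered statistically significant". The pair is not mentioned.

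**The concern.** Every woman at a given station is in the same arm. Any difference between stations in staff, local poverty or referral practice is therefore part of the arm difference, and more women per station do not average it away. The information on that variation comes from four stations: 2 df for an unpaired comparison, 1 df for a paired one.

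A design effect built on groups of 10 does not contain this variance. E-TAU is described as medication and referral, without therapy groups, so a group size of 10 does not clearly describe that arm either.

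Two things are at stake. Readers may take 85% power at face value and misread a null result. And if adjustment in practice stops at the group, P values may be too small and intervals too narrow.

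**Working it through.** **Inputs.** From the article: 4 stations, 2 per arm; 166 enrolled (166/4 = 41.5 per station); 64 per arm retained (128 in total, 32 per station); ICC 0.1 and cluster size 10 for groups; d = 0.3 and 0.4; power 0.85; two-sided alpha 0.05. Assumed: site ICC from 0 to 0.1, equal station sizes, total variance 1.

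**1. The plan's own figure.** The group design effect is 1 + (10 − 1) × 0.1 = 1.9, against a stated value of at least 2. The number per arm without clustering is 2 × (1.960 + 1.036)² / d².
- d = 0.4: 112.2, so 113 per arm and 226 in total; about 430 with design effect 1.9 and 452 with 2.
- d = 0.3: 199.5, so 200 per arm and 400 in total; 760 with design effect 1.9 and 800 with 2.

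The stated 142 is not reproduced. At design effect 1.9, 142 women give power of about 0.41 (d = 0.4) or 0.25 (d = 0.3). So the 85% does not follow even at group level.

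**2. Design effect at site level.** If the plan's 0.1 applied to stations: 1 + 40.5 × 0.1 = 5.05 as enrolled, or 1 + 31 × 0.1 = 4.10 as retained.

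**3. Power at site level.** SE = √(4 × DE / 128) with DE = 1 + 31 × ICC. The noncentrality is 0.4 / SE. The critical t is 4.30 on 2 df and 12.71 on 1 df.

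| Site ICC | DE | SE | 0.4/SE | Power, 2 df | Power, 1 df |
|---|---|---|---|---|---|
| 0 | 1.00 | 0.177 | 2.26 | 0.26 | 0.14 |
| 0.01 | 1.31 | 0.202 | 1.98 | 0.21 | 0.12 |
| 0.05 | 2.55 | 0.282 | 1.42 | 0.14 | 0.09 |
| 0.1 | 4.10 | 0.358 | 1.12 | 0.11 | 0.08 |

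The 1-df column assumes that pairing removes no site variance. If it removed all of it, power would be about the 0.14 of the first row.

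**4. Can more women help?** As N grows, 4 × DE / N tends to the site ICC, so SE tends to √ICC. At d = 0.4 on 2 df, power then tends to 0.56 at ICC 0.01, 0.19 at 0.05 and 0.12 at 0.1. At these ICCs no sample size within four stations reaches 85%.

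**5. Type I error with clustering by group only.** The layout is 4 stations × 4 groups × 8 women (128), tested with a group-level t on 14 df; this layout is an assumption. For site ICC 0.05 and group ICC 0:
- True variance of the arm difference: 2 × (0.05/2 + (0.95/8)/8) = 0.0797.
- Expected variance estimate: 2 × (0.95/8 + 0.05 × 4/7)/8 = 0.0368.
- The SE is too small by √(0.0797/0.0368) = 1.47, so the critical value 2.145 acts like 2.145/1.47 = 1.46. The two-sided tail area is about 17%.

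Simulated null trials agree. With group ICC between 0.1 and 0, type I error is about 5% at site ICC 0, 7-8% at 0.01, 8-10% at 0.02 and 13-17% at 0.05. These figures assume that matching removes no site variance.

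**The case against.** **Site is in the analysis text.** A reader who stops at the words on group clustering might infer that the planned analysis ignores the stations. It does not: the sentence names cohort and site. What stands is that only group clustering is described as the adjustment, with no reference distribution for four clusters.

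**The error rate depends on the method.** A reader might infer a false-positive rate near 25%. That figure belongs to a site-robust sandwich SE with a normal reference, which the plan does not name. A likelihood mixed model with random site and group intercepts and a 1.96 cut-off, simulated on the same layout, gave 3-5% at site ICC 0, 6% at 0.01, 7-8% at 0.02, 10-11% at 0.05 and 13-15% at 0.1. That is milder but still inflated as site variance grows. Whether the plan intends those random intercepts is not stated.

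**The pair.** A reader might infer that leaving out the pair causes the inflation. It works the other way: if matching succeeds, ignoring the pair makes the test conservative. When pairing removes all site variance, the unpaired site test falls to 0.02-0.04. The omission is a departure from the stated design and no more.

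**Unseen detail and stated limits.** Degrees of freedom, a pair term and a partially nested model for the therapy groups may be fixed in an analysis plan that is not shown. The article also admits possible confounding at cluster level, disclaims effects equivalent to a randomized trial, and limits generalizability to four urban stations. All this stands, and it is why the tests cannot be called certainly anticonservative. None of it repairs the power statement, which the article makes itself on the wrong unit.

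**Conclusion.** The power statement is wrong as written. It omits the allocated unit, and at d = 0.4 with 128 retained a site-level test has power of about 0.26 to 0.11 (2 df) or 0.14 to 0.08 (1 df) over site ICCs from 0 to 0.1, against 0.85 stated. Even at site ICC 0 the shortfall is large, so this conclusion does not depend on the assumed ICCs.

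The point on testing is weaker. The .05 rule is likely to be anticonservative if site variance is not zero and adjustment is by group only. The size depends on a site ICC that the article does not give, on how far matching worked, and on a small-sample method that may be set elsewhere.

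**What to change.** 1. Restate the Power Analysis section. Say that its design effect ignores the four allocated stations, show the site-level design effect for a range of ICCs (5.05 for 41.5 per station or 4.10 for 32 retained, if 0.1 applied to stations), and withdraw or restate the 85%.
2. Beside the individual-level mixed model, report the primary contrast from station means with a small-sample t reference. Use 2 df if unpaired or 1 df if the pair is included. The two cannot be combined, because a pair effect takes one of the two df; choose one before the arms are compared.
3. State that individual-level P values and confidence intervals are conditional on these four CHSs.

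Data collection is complete and the analysis is described as in progress, so the cost is wording and one small added analysis. The downside is that fewer results can be called statistically significant and the stated power becomes less favourable.
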